### Sample Size

A formal sample size calculation is not appropriate for a feasibility trial. A previous audit of trials registered in the Clinical Research Network database in the United Kingdom found that most feasibility and pilot trials had a median of 30 or 36 participants per arm and the researchers recommend an upper limit of 60 participants for a feasibility trial [16]. Therefore, a target of 60 dyads is set for this study, leading to 30 dyads per treatment arm.

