#### Blinding

This trial will include both blinded and unblinded researchers at each local site. It is not possible to blind the participants to their treatment arm as the iCST app is a nonpharmacological intervention. However, each study site will include at least one researcher kept in ignorance of study allocations. The baseline assessment can be performed by either researcher. However, both follow-ups will be completed only by the researcher who is unaware of the randomization outcome for each dyad. If disclosure does occur, this will be recorded by the visiting researcher along with details on how it occurred. The unblinded researcher will perform the randomization, communicate the outcome with the participants, and for the experimental group, install the iCST app, provide weekly telephone support calls, and complete the usability and acceptability questionnaire at the end of the study. Furthermore, the unblinded researcher will not be informed about the results of the assessments.

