### Training and Adherence

In order to ensure treatment integrity for all participants, individual study sites will receive a demonstration of the iCST app along with training in its installation and use prior to the start of recruitment. Dyads in the experimental group will receive an in-home visit from the unblinded researcher who will install the app and explain how it works using a short supplementary document containing instructions with screenshots of the app. Furthermore, all dyads will receive weekly telephone support calls from the same unblinded researcher in order to monitor adherence and to track the overall progress and any challenges or technical difficulties with using the iCST app. Phone calls will be completed with the carer and all questions will be included on a standardized telephone sheet. The questions relate to general experience, number of sessions completed in a week (on average), amount of time spent per session (on average), enjoyment, and any likes/dislikes. Any reason for not being able to use the iCST app over the week will also be recorded on the telephone sheet.

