### Adverse Events

Previous work with CST, maintenance CST, and iCST has not documented any harmful side effects nor any serious adverse events from participating in the intervention activities [1,2,34]. Given that the iCST app is based on the principles of CST and follows a comparable structure to iCST, it is expected that this study will not lead to harmful side effects for either the person with dementia or the carer. Researchers will be made aware of any adverse events during follow-up assessments or the weekly telephone support calls. The trial manager and chief investigator of the study will be informed in case of any adverse events, and they will assess the severity of the adverse event. Serious adverse events include death, illness related to a previous health condition, or hospitalization.

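### The definition of a serious adverse event includes a category with no threshold of seriousness, so the count will mix background illness with serious events

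*Protocol article*

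**What the plan says.** The Adverse Events section of the protocol article defines seriousness in one sentence: "Serious adverse events include death, illness related to a previous health condition, or hospitalization". It says that the trial manager and chief investigator are told of any adverse event and that "they will assess the severity of the adverse event".

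The same section reports that earlier work with related therapies "has not documented any harmful side effects nor any serious adverse events from participating in the intervention activities". From this it concludes that "it is expected that this study will not lead to harmful side effects for either the person with dementia or the carer".

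On how events come to light, it says: "Researchers will be made aware of any adverse events during follow-up assessments or the weekly telephone support calls". Two other sections describe those calls. Blinding lists the tasks of the unblinded researcher, among them: "for the experimental group, install the iCST app, provide weekly telephone support calls". Training and Adherence says that "all dyads will receive weekly telephone support calls from the same unblinded researcher".

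**The concern.** Two of the three listed items are outcomes. The third is a statement about origin: it asks whether an illness has a link to something the person already had, and not how bad the illness was. A brief flare of a chronic complaint meets the wording and would be tabulated beside a death.

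The category also points away from what a safety table should show. Harm from a tablet app would more naturally appear as something new, whereas a link to an earlier condition suggests a background cause. In an older population with chronic disease, such illness may be common over 11 weeks.

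At stake is how the serious event table is read when the investigators decide on a full-scale trial. A large count could be mistaken for a safety signal. If the control arm is asked less often, the app arm could show an excess that comes only from more frequent contact. A full-scale protocol could also inherit the definition.

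**Working it through.** The point is about wording, so the main check is a reading. The arithmetic below only shows direction and scale.

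**1. The listed items against what seriousness should capture.**

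| Listed item | Describes | Threshold of gravity |
|---|---|---|
| Death | outcome | yes |
| Hospitalization | outcome | yes |
| Illness linked to an earlier condition | origin | none |

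No other sentence in the section limits the third item. The severity assessment does not do so: an event can be mild in severity and still fall in the category.

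**2. Who is exposed to the category.** Eligibility Criteria requires a dementia diagnosis and an age of 50 or over with no upper limit. TAU Group notes that some participants may be taking acetylcholinesterase inhibitors. Existing conditions are therefore to be expected. Whether ordinary worsening of the dementia itself would count is unclear from the wording, and the point does not depend on it.

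**3. The sections on the calls, side by side.** Blinding ties the calls to the experimental group. Training and Adherence says all dyads, but describes calls about sessions completed, time spent and difficulties with the app, which have no counterpart under usual care. If only the app arm is called, the scheduled occasions to report an event over 11 weeks are:

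- app arm: about 11 calls + 2 follow-ups = 13
- control arm: 2 follow-ups

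Minor illness is what a weekly call would pick up and a visit weeks later could miss. Deaths and hospitalizations should depend less on the number of contacts.

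**4. Stated sample size.** Sample Size says "a target of 60 dyads is set for this study, leading to 30 dyads per treatment arm". 60 / 2 = 30, which agrees. The article gives no figure for adverse events.

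**5. What 30 per arm could show under a clean definition.** With no events in n units, the one-sided 95% upper bound on risk is 1 − 0.05^(1/n). For n = 30 dyads: 1 − 0.05^(1/30) = 0.095, or 9.5%.

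**6. Direction of the dilution (assumed rates; the documents give none).** Let b be the background risk of an event classed as serious, and suppose the app adds a 10% risk among those otherwise free of one. The app-arm risk is t = b + 0.10(1 − b), the background share of app-arm events is b/t, and the standard error of the risk difference with 30 per arm is √{[b(1 − b) + t(1 − t)]/30}.

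| Assumed b | t | Difference t − b | Background share b/t | Standard error | Difference / standard error |
|---|---|---|---|---|---|
| 0.02 | 0.118 | 0.098 | 17% | 0.064 | about 1.5 |
| 0.10 | 0.190 | 0.090 | 53% | 0.090 | 1.0 |
| 0.30 | 0.370 | 0.070 | 81% | 0.122 | about 0.6 |

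A broader definition raises b. The background share then climbs and the contrast between arms weakens. Even at the lowest assumed background, the difference is only about 1.5 standard errors.

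**The case against.** The strongest reply is that the article's safety paragraph is brief background, that safety is not among the study aims or feasibility outcomes, and that most of what one might build on this sentence goes beyond the text. Much of that stands.

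- A reader might infer that a life-threatening event or lasting disability managed at home would be missed. The sentence says what serious events include and does not close the list, so this is not supported.
- A reader might infer that events are judged for severity and nothing else. The article names severity but does not say that it is the sole judgement. A journal article commonly leaves relatedness and form fields to the full protocol, so their absence here is no finding.
- A reader might infer that the count cannot measure harm. Deaths and hospitalizations are counted, and background illness is expected in both randomized arms. The broad category dilutes a comparison between arms but does not abolish it.
- A reader might infer that a planned test of no harm is defeated. None is planned: Statistical Analyses calls significance testing inappropriate, and the 9.5% bound shows that sample size limits the inference under any definition.
- Data collection ended in March 2020, so new wording cannot change what was captured.

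What the reply does not answer is the listed item itself. Leaving detail to a fuller document explains silence, but not a printed criterion that classes minor illness as serious. An open list does not help either, because the problem is an item on the list. The reassurance from the control arm also depends on equal capture, which the two descriptions of the calls leave in doubt.

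**Conclusion.** The point holds in a limited form. The definition contains a criterion of origin with no threshold of seriousness. Applied as written, it classes minor illness linked to an existing condition as serious, and the resulting count is weak evidence on the stated expectation of no harm.

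The size cannot be given, because the documents contain no illness rate and do not show how literally sites applied the definition. One could assume a rate and multiply it by the number of people recruited, but the result would only restate the assumption. The dilution table is likewise an illustration on assumed risks, with the dyad as the unit.

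A difference in capture between arms is conditional: it arises only if the weekly calls went to the app arm alone. The article supports two readings, and this review does not settle which was followed. The defect touches the safety description and not the feasibility or clinical outcomes.

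**What to change.** 1. Remove the category based on a previous condition from the definition, and classify an event as serious by its outcome, for both members of the dyad. Death and hospitalization stay. Other outcome criteria, such as threat to life or lasting disability, can be named so that the list is explicit.
2. Reclassify the logged events once from their descriptions before reporting, preferably without sight of allocation. The article says that analyses were still in progress, so this can be done. State how many events could not be reclassified from the record.
3. Report serious events by arm. Keep seriousness separate from severity and, where the record allows, give relatedness as a third item.
4. Reconcile Blinding with Training and Adherence on who received the weekly calls, and report what was done. If only the app arm was called, say so beside the table and, where recorded, show whether each event surfaced on a call or at a follow-up visit.
5. Carry the corrected definition into any full-scale protocol.

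The cost is a little review time per event and a few lines in the report. No new data are needed, but reclassification can be no better than the event descriptions that were kept.

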### Data Security and Entry

Each study site will create their own password-protected spreadsheet containing participant identifiable information and allocation outcome for the dyad. This spreadsheet can only be accessed through a secure NHS Trust computer. After collection of the data from each site, the data will be stored in a secure cabinet at the University of Nottingham. Identifiable information, including the consent forms, will be kept in a separate locked cabinet. After reviewing the data and checking the scoring, it will be entered manually into SPSS version 25 (IBM Corp) for Windows, which will be used for all the analyses.

### Statistical Analyses

Key feasibility outcomes will be reported through frequencies and will include the number of participants screened, recruited, randomized, and retained through the duration of the trial. Adherence to the intervention will be assessed by calculating the average number of iCST app activities completed by the dyad logged in the weekly telephone calls. The usability and acceptability of the iCST app will be further investigated by examining data from the weekly telephone calls, posttrial interviews, and by calculating scores on the Questionnaire of Usability and Acceptability, with higher scores indicating higher levels of usability and acceptability. Data from the posttrial interviews will be coded and summarized and may be analyzed thematically with specialized software if sufficient data have been obtained to reach data saturation [35]. Lastly, outcome measures will be assessed for appropriateness by calculating missing data rates within the measures and across the follow-ups. As this is a feasibility trial and null hypothesis significance testing is inappropriate due to a likely lack of power to detect significant effects of the intervention [36-38], analyses will mainly include descriptive statistics computed for each group and outcome measures, including means, standard deviations, 95% confidence intervals, and effect sizes [12,39]. However, in order to compare the outcomes on each of the questionnaires between the 2 groups, an analysis of covariance will be undertaken, which will help to better understand any trends in the data. All analyses will be based on the intention-to-treat principle in that all available data will be included in the analyses. Rules for missing data will be adapted from the main iCST trial [2]. Data will not be imputed if outcome measures or assessments are missing in full, and imputation (using prorating) will only be used when fewer than 20% of cases are missing on any given measure.

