**Results:**

This study received funding in May 2015 and obtained ethical approval in March 2018. Data collection began in November 2018 and was completed in March 2020 with a total of 61 dyads recruited. Data analyses are in progress and the final results are expected to be available in the spring of 2021.

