**Measures**
Cognition measured using the Alzheimer’s Disease Assessment Scale-Cognitive Subscale [23].Quality of life measured using the Quality of Life-Alzheimer’s Disease (QoL-AD) questionnaire [24]. Carers will complete the family version of the QoL-AD.Health-related quality of life measured using the EuroQoL 5-dimension questionnaire [25].Relationship quality measured using the Quality of the Carer-Patient Relationship questionnaire [26].Symptoms of depression measured using the Cornell Scale for Depression in Dementia [27]. Carers will complete this questionnaire as an informant.Behavioral disturbances measured using the Neuropsychiatric Inventory and will be rated by the carer only [28].Functional abilities measured using the Bristol Activities of Daily Living Scale [29] and rated by the carer only.

Outcome measures for carers.

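### As written, the 20% prorating limit counts participants with missing data on a measure, not the items one participant left blank, so it does not control the quality of a prorated score

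*Protocol article*

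**What the plan says.** The Statistical Analyses section of the protocol article sets two conditions on imputation. The first excludes wholly absent data: "Data will not be imputed if outcome measures or assessments are missing in full". The second fixes a numerical limit and its unit: "imputation (using prorating) will only be used when fewer than 20% of cases are missing on any given measure".

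On the origin of these conditions the section says "Rules for missing data will be adapted from the main iCST trial", without restating that trial's rules. It also says "All analyses will be based on the intention-to-treat principle in that all available data will be included in the analyses", and that "outcome measures will be assessed for appropriateness by calculating missing data rates within the measures and across the follow-ups".

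The article nowhere defines a case in another sense, and it gives no minimum number of items that a person must have answered. On numbers, the Sample Size section says that "a target of 60 dyads is set for this study, leading to 30 dyads per treatment arm". The abstract reports that data collection was "completed in March 2020 with a total of 61 dyads recruited".

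**The concern.** Prorating replaces a person's missing items using the items that the same person answered. What makes a prorated total trustworthy is the share of the form that person completed. How many other participants have gaps on the same measure has no bearing on it.

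A limit counted over participants therefore fails in two directions. It can let through a total that rests on very few answers, because few other people have gaps. It can also withhold prorating from someone who missed one item, because many others also missed one. The second outcome sits badly with the commitment to include all available data.

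The scores concerned feed the means, standard deviations, confidence intervals and effect sizes reported by group, and the analysis of covariance on each questionnaire. The article intends these findings to inform a full-scale trial.

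**Working it through.** The article gives no figure of its own to reproduce here. The check applies the stated limit literally.

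**Inputs from the article.** The limit is fewer than 20% of cases on a measure. N = 60 dyads planned (Sample Size) and 61 recruited (Abstract, Results). The only within-person limit is the exclusion of wholly missing measures.

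**Assumptions, because the article gives none.** K is the number of items on a scale and q is the chance that any one item is blank, independent across items and people. All N cases are taken as assessed, and a case counts as missing on a measure if at least one item is blank.

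**Step 1: where the limit falls.**
- N = 60: 11/60 = 18.3%, so prorating is allowed. 12/60 = 20.0% is not below 20%, so it is barred for everyone on that measure.
- N = 61: 12/61 = 19.7%, allowed. 13/61 = 21.3%, barred.

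**Step 2: what is permitted below the limit.** With 11 of 60 cases incomplete, the text does not stop any of the 11 being prorated from a single answered item. That is 1/10 = 10% of a 10-item form, or 1/30 = 3% of a 30-item form.

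How good such a total is can be gauged with an equal inter-item correlation r. The correlation between the mean of m answered items and the mean of all K is √(v_K / v_m), where v_m = (1 + (m − 1)r)/m, and v_K is the same with K in place of m.
- Example: K = 13, r = 0.3, m = 1. v_13 = (1 + 12 × 0.3)/13 = 0.354 and v_1 = 1, so the correlation is √0.354 = 0.595.
- For K of 10, 13 and 20 and r from 0.2 to 0.5, a total from one answered item correlates 0.49 to 0.74 with the full score.
- With a limit of fewer than 20% of items missing within the person, at most 1 of 10, 2 of 13 or 3 of 20 items may be missing. A total at that limit correlates 0.98 to 0.996 with the full score over the same range of r.

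**Step 3: what is lost above the limit.** If 12 of 60 people each miss one item, their forms are 90% complete (K = 10) to 97% complete (K = 30). None may be prorated, and 12/60 = 20% of totals are lost on that measure.

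**Step 4: how likely the bar is.** The chance that a person misses at least one item is π = 1 − (1 − q)^K. The chance that prorating is barred is P(Bin(60, π) ≥ 12).
- Example: K = 13, q = 2%. π = 1 − 0.98^13 = 0.231, and P(Bin(60, 0.231) ≥ 12) = 0.76. The expected number with any gap is 60 × 0.231 = 13.9. About 12.2 of these miss exactly one item (60 × 13 × 0.02 × 0.98^12).

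| Items (N = 60) | q = 0.5% | q = 1% | q = 2% |
|---|---|---|---|
| 10 | about 0 | 0.01 | 0.42 |
| 13 | about 0 | 0.06 | 0.76 |
| 20 | 0.01 | 0.41 | 0.99 |
| 30 | 0.12 | 0.89 | about 1 |

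With N = 61 the bar starts at 13 cases. At q = 2% the chances are then 0.32 (10 items), 0.68 (13 items) and 0.99 (20 items).

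**Step 5: does another reading of a missing case rescue the rule?** If it means a wholly blank form, that form is excluded by the first condition and has no answered items to prorate from. Whether other people's partly completed forms may be prorated would then depend on how many forms were absent. There would still be no limit within the person.

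**The case against.** The strongest reply is that the word for participants may be a slip for items. The sentence names prorating and sets aside wholly missing measures, so it reads most coherently as a limit on items. The source rules, in the main iCST trial, are not shown. This is a fair account of how the sentence may have arisen. It does not remove the point: nothing in the article corrects the unit, and the adapted rule is the one printed. Nor is this a detail left to a fuller document, since the article itself fixes the threshold and its unit.

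The likelihood figures rest on assumed item counts and non-response rates. That stands. The article describes home interviews, spread over two days if needed, and a review of data and scoring before entry. Both could keep item non-response low. At 0.5% the bar is improbable for scales of up to 20 items.

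Three stronger readings are tempting, and the article does not support them.
- A reader might infer that the rule will impute near-empty forms and discard near-complete ones. The wording makes the 20% a necessary condition. It permits prorating below the limit and does not require it. The literal text could produce these outcomes; it does not say that it will.
- A reader might infer that the rule commits the trial to prorating the measure described as "Health-related quality of life measured using the EuroQoL 5-dimension questionnaire", and that this would be invalid. The article names the instrument without saying how it is scored. The phrase about any given measure says where the threshold is counted, not that every measure will be prorated.
- A reader might infer that the conclusion on acceptability of the measures is distorted. Missing-data rates are a separate planned output, and nothing says that they are counted after prorating.

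**Conclusion.** The rule is wrong as written: it sets the prorating limit on the wrong unit and leaves no within-person limit short of a wholly missing measure. That conclusion needs no assumption beyond the literal text and what prorating does. The cut-offs of 11 and 12 cases (12 and 13 with 61 dyads) assume that all recruited dyads are assessed, and they fall if some are lost.

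The practical size is uncertain. The chance that prorating is barred on a measure runs from negligible to near certain over plausible scale lengths and item non-response of 0.5% to 2%, assuming independent gaps.

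The consequence is moderate. Analyses are mainly descriptive, the analysis of covariance is exploratory, and no formal sample size calculation rests on these scores. Recruitment, retention and the adherence benchmark do not use prorated scores. This should be fixed, but it does not threaten the trial's main feasibility conclusions.

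**What to change.** Replace the clause on prorating with: *A participant's scale score is prorated from the answered items only when fewer than 20% of that participant's items on the scale are missing; otherwise the score is treated as missing.*

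Add that the planned missing-data rates are calculated before any prorating, so that their basis is explicit.

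The cost is one or two sentences in the analysis text and a small change to the scoring syntax. No new data are needed, and the article reports that data cleaning, entry and analysis were still under way.
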